| Target Patients       | Patients with severe lower limb ischemia who require bypass surgery with peripheral anastomosis to the calf artery or foot artery below the knee, but who do not have an appropriate autologous vein.                                                                                                                                                                                                                                                                                                                                                                                                                                                                                                                                                                                                                                                                                                                                                                                                                                                                                                                                                                                   |
| Inclusion criteria    | 
 
1. Agreement for participating in the study and informed consent signed by the patient.
 
2. Age is over 18 years old.
 
3. Lower limb ischemia that meets grade 3 or 4 (<math>ABI^* < 0.6</math>, <math>SPP < 40</math> mmHg) in Wifi classification of CLTI.
 
4. Patients correspond to one of the following. 
 
(a) GLASS classification of GVG is stage III, and corresponds to clinical stage 2, 3 or 4 of Wifi classification.
 
(b) GLASS classification is stage II, and corresponds to clinical stage 3 or 4 of Wifi classification.
 
(c) GLASS classification is stage I or II, and clinical symptoms do not improve even if intravascular treatment is performed.
 
 
 
5. Upper or lower limb veins of the optimal length and diameter required for bypass surgery does not exist.
 
6. Patients with arterial occlusion on the proximal side of the planned proximal anastomosis site for bypass surgery.
 
7. Survival of 12 months or more and followed-up for 12 weeks after bypass surgery are possible.
 
 |

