#### 4.2 Selection Criteria

- (1) Patients who have given written consent to participate in the clinical trial
- (2) Patients who are 18 years of age or older at the time of consent
- (3) Patients with severe lower limb ischemia who meet the comprehensive WIfI classification of chronic limb threatening ischemia (CLTI) severity criteria (reference 15) of ischemia grade 2 or 3 (ABI <0.6, SPP <40 mmHg)
- (4) Patients who are recommended to undergo lower limb artery bypass surgery and who meet any of the following criteria:
  - a: Stage III limb ischemia according to the Global Anatomic Staging System (GLASS) classification of the Global Vascular Guideline (GVG) (Reference 8) and clinical stage 2, 3, or 4 according to the WIfI classification
  - b: GLASS stage II limb ischemia and clinical stage 3 or 4 of the WIfI classification
  - c: GLASS stage I or II limb ischemia in which sufficient blood flow cannot be achieved even with endovascular treatment (including clinical failure in which the wound does not heal and clinical symptoms do not improve)
- (5) Patients who do not have an appropriate upper or lower limb vein (or lower limb vein in the case of dialysis patients) that meets the length and diameter ( $\geq 3$  mm) required for bypass surgery (References 16 - 18) and has no abnormal findings such as aneurysm
- (6) Patients who require peripheral anastomosis of a bypass to a calf artery below the knee or a foot artery
- (7) Patients who are judged to be able to survive for  $\geq 12$  months and be able to be followed up for 12 weeks after bypass surgery at the time of obtaining informed consent

[Rationale for setting]

- (1), (2), (7) To select appropriate patients from ethical and safety standpoints
- (3) To select patients who require revascularization
- (4) To select patients who are best suited to bypass surgery when selecting a treatment method
- (5) To select patients who do not have a suitable autologous vein for a bypass graft
- (6) Because existing artificial blood vessels cannot be used as a bypass graft in this area

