#### 4.3 Exclusion criteria

- (1) Patients whose general condition makes it difficult to secure the implantation period of the test device required for biotube formation due to reasons such as the need for immediate revascularization.
- (2) Patients whose general condition makes it difficult to tolerate surgery due to severe malnutrition (CONUT score 8-12) (Reference 19) or severe complications, etc.
- (3) Patients who may not be able to secure two or more implantation sites for the test device due to reasons such as poor skin condition or a history of exposure to subcutaneous implants in the past.
- (4) Patients who had undergone invasive surgery within 30 days prior to enrollment (excluding those undergoing treatment for leg wounds)
- (5) Patients who do not have a peripheral target artery required for bypass surgery or who have a history of endovascular treatment at the site of the proposed peripheral anastomosis
- (6) Patients who have arterial occlusion proximal to the planned central anastomosis site for bypass surgery
- (7) Patients who cannot confirm blood circulation distal to the planned peripheral anastomosis site of bypass surgery (excluding those who can confirm collateral circulation)
- (8) Patients who have had a lower limb amputation proximal to the midfoot
- (9) Patients with a history of or comorbid malignant tumors (excluding those who have had no recurrence or new onset for more than 5 years after treatment)
- (10) Patients who are using immunosuppressants due to comorbid autoimmune diseases or after transplantation, etc.
- (11) Patients with a history of allergies to stainless steel or polyolefin resins
- (12) Patients who are pregnant or may be pregnant
- (13) Patients who are participating or planning to participate in other clinical trials or interventional clinical studies
- (14) Patients who are judged by the investigator or co-investigator to be inappropriate for this clinical trial due to medical condition or safety reasons.

[Rationale for setting]

- (1), (2), (4), (9)-(12) To ensure the safety of subjects
- (3), (5)-(8) To properly evaluate the efficacy and safety of the test device
- (13), (14) To conduct the clinical trial ethically and safely

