### 9.1 Analysis population

(1) Efficacy analysis subjects

1) FAS (Full Analysis Set)

The analysis population consisting of registered subjects excluding the following subjects will be the FAS:

- Subjects who were not critical limb ischemia patients targeted by this clinical trial
- Subjects who have never used the investigational device
- Subjects with no efficacy data after registration

2) PPS (Per Protocol Set)

The PPS will be the analysis set consisting of subjects from the FAS, excluding the following subjects:

- Subjects who do not meet the inclusion criteria
- Subjects who meet the exclusion criteria
- Subjects who meet other regulations in the clinical trial protocol that may affect the efficacy evaluation.

The case review committee will also discuss how to handle discontinued cases.

(2) Safety Analysis Set

The analysis set consisting of the subjects who were enrolled, excluding the following subjects, will be the Safety Analysis Set (SAS):

- Subjects who have never used the test device
- Subjects who have no safety data after enrollment

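### Synopsis inclusion criteria 6 and 3 conflict with Section 4: item 6 requires a condition the protocol excludes, and the ischemia grade ranges differ

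*Protocol*

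**What the plan says.** The eligibility criteria appear twice in the protocol: in the overview table at the front and in Sections 4.2 and 4.3.

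**Item 6.** The overview's inclusion and exclusion lists carry the same sixth entry, word for word: "Patients with arterial occlusion on the proximal side of the planned proximal anastomosis site for bypass surgery". Section 4.2(6) is a different condition: "Patients who require peripheral anastomosis of a bypass to a calf artery below the knee or a foot artery". In Section 4, upstream occlusion appears only as an exclusion, at 4.3(6): "Patients who have arterial occlusion proximal to the planned central anastomosis site for bypass surgery".

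**Item 3.** The overview has "Lower limb ischemia that meets grade 3 or 4" on the WIfI classification. Section 4.2(3) has "ischemia grade 2 or 3 (ABI <0.6, SPP <40 mmHg". The overview attaches the same ABI and SPP limits to its own range.

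**Where the criteria are used.** The opening paragraph of Section 4 defines a trial subject as someone who satisfies every criterion in 4.2 at registration and breaches none in 4.3. Section 6.2 (screening) refers to the inclusion and exclusion criteria without a section number. Section 4.4(4) discontinues a subject found after enrolment not to meet the eligibility requirements, and the overview repeats that rule. Section 9.1 removes from the PPS "Subjects who do not meet the inclusion criteria", and also those who meet an exclusion criterion, again without saying which list is meant.

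**The concern.** An inclusion criterion identical to an exclusion criterion cannot be intended, and two grade ranges cannot both be the right label for one pair of measured limits. The overview is the part of a protocol most often used for quick reference at screening, so an error there can reach practice even when the body text is sound.

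Three decisions depend on which list is read: whether a patient is registered, whether an enrolled subject is later discontinued as ineligible, and whether a subject counts in the PPS. The second can arise after surgery, since Section 6.4.2 provides for 2 to 4 devices to be implanted once registration is complete. With a target of 12 subjects, a single inconsistent classification would be visible in the per-protocol results.

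**Working it through.** No figure in the plan bears on this point, so the check sets the texts side by side.

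**Item 6.** Let A be occlusion upstream of the planned proximal anastomosis, and D the need for a distal anastomosis to a below-knee calf artery or a foot artery.

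| Source | Inclusion 6 | Exclusion 6 | Jointly |
|---|---|---|---|
| Overview lists | A | not A | cannot be satisfied |
| Sections 4.2 and 4.3 | D | not A | can be satisfied |

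- A patient without upstream occlusion fails overview inclusion 6, but nothing in item 6 of either Section 4 list bars that patient if D holds.
- A patient with upstream occlusion passes overview inclusion 6 and is excluded by overview exclusion 6 and by 4.3(6).
- D is absent from the overview's numbered inclusion list. It is not absent from the overview, because the Purpose and Target Patients rows both state it.

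Both overview entries are complete, numbered and in sequence, so this is not damage from text extraction.

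**Item 3.** The overview's set of grades is {3, 4} and that of Section 4.2(3) is {2, 3}. Their intersection is {3}. Grade 2 qualifies only under Section 4.2, and grade 4 appears only in the overview. The limits attached are the same in both places (ABI <0.6, SPP <40 mmHg). The WIfI category scores are recorded at eligibility confirmation (Section 6.5.1(11)), so the grade will be in the data and can be compared with either list.

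**Which list governs.** The opening of Section 4 names 4.2 and 4.3. It does not say that they prevail over the overview, and Sections 6.2, 4.4(4) and 9.1 do not point back to it.

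**The case against.** The strongest answer is that the operative text is already fixed. Section 4 opens by tying eligibility to 4.2 and 4.3, those sections are consistent with each other on item 6, and 4.4(4) sits inside Section 4 and is most naturally read as referring to it. The PPS rule can be read the same way, and individual cases go to a case review meeting before data fixation (Section 9). On the grade, a site that applies only the measured limits would admit the same patients under either label.

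Most of this stands. It defeats two inferences a reader might draw:

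- **That no patient can qualify, so the PPS must be empty.** This follows only if the overview's lists override the opening of Section 4, and nothing in the protocol says they do.
- **That each grade 2 subject shifts the trial by 1/12 = 8.3%.** The protocol neither defines the grades against the limits nor says how many grade 2 subjects to expect, so this is one subject as a share of the target and not an estimate of impact.

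The answer does not remove the conflict. The screening and PPS rules cite no section, and Section 6.2 also requires a third party's opinion on eligibility, so two people working from different pages could reach different answers. Leaving the matter to the case review meeting means choosing the governing list after the subjects' data are known.

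**Conclusion.** The concern holds as a consistency error. The overview's inclusion item 6 is wrong as written: it demands what the overview's exclusion list and Section 4.3(6) rule out, and it stands where 4.2(6) places the distal-anastomosis requirement. The ischemia grade ranges in overview item 3 and Section 4.2(3) disagree while sharing the same ABI and SPP limits.

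The trial can enrol, because Section 4 can be satisfied and is the text named for eligibility. The consequence is a risk of inconsistent screening, of discontinuation under 4.4(4) and of inconsistent PPS membership. Its size cannot be stated from the protocol, which does not show which list sites used or how many subjects would fall in the disputed grades. No endpoint, sample size or analysis method changes. The conclusion rests on the two texts alone and uses no outside definition of the grading scale. It takes no position on which grade range is right.

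**What to change.** 1. Reconcile overview inclusion item 6 with Sections 4.2(6) and 4.3(6), so that no condition is both required and excluded and the numbered list carries the distal-anastomosis requirement.
2. Reconcile the ischemia grade between overview item 3 and Section 4.2(3), so that a single range accompanies ABI <0.6 and SPP <40 mmHg. The investigators must decide the range.
3. Have Sections 6.2, 4.4(4) and 9.1 cite Sections 4.2 and 4.3 explicitly.
4. Check that the registration procedure and the subjects already registered were assessed against Section 4, and document any who were not before data fixation.

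The cost is two corrected lines and three cross-references in the next amendment, with the approvals that Section 14.2 already requires, plus a short review of registration records.

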## 1. Development history

### 1.1 Background of the clinical trial plan

Severe limb ischemia presents with ischemic rest pain, foot ulcers, gangrene, etc., and in Japan, approximately 10,000 patients undergo amputation annually. The prognosis after amputation is extremely poor, with a 1-year mortality rate of 25% and a contralateral amputation rate of 25%, making it a life-threatening condition (References 1, 2). If revascularization is not possible, the patient will have to amputate the lower limb.

Revascularization of the lower limbs is generally performed by endovascular therapy, which is a catheter treatment, or bypass surgery using autologous veins or artificial blood vessels (Reference 3). Endovascular treatment of the popliteal artery below the knee to the calf artery often results in restenosis or occlusion, and bypass using thin artificial blood vessels also has poor results (References 4-6), and bypass using autologous veins has the best results (References 7, 8). However, if autologous veins cannot be used due to reasons such as varicose veins, thin veins, or the veins having already been used for bypassing the coronary arteries or peripheral arteries, limb salvage becomes difficult.

There is a long and thin artificial blood vessel that can be used for below-knee bypass. Although artificial blood vessels made of synthetic materials such as ePTFE (expanded polytetrafluoroethylene) and PET (polyethylene terephthalate) have shown satisfactory results in terms of patency and durability for large diameters (10 mm or more), they are insufficient for medium diameters (6-8 mm), and there are no satisfactory products for small diameters (5 mm or less) used for lower limb peripheral bypass or coronary artery bypass. A practical artificial blood vessel made from biomaterials or using conventional tissue engineering has not yet been completed. By using in-Body Tissue Architecture (iBTA) developed by [name], a thin and long autologous tubular tissue (biotube) that can be used for below-knee bypass can be created by subcutaneously implanting a mold for 1-2 months (References 9-13). The BioTube enables surgical revascularization for patients with severe lower limb ischemia, who were previously unable to undergo revascularization, and is expected to improve the pathology of insufficient circulation below the knee and achieve long-term patency through autologous revascularization. This test device was designated as a medical device under the Sakigake Designation System of the Ministry of Health, Labor and Welfare in fiscal year 2019, and is classified as a new medical device of class III. With support from the Medical Engineering Collaboration Project of the Japan Agency for Medical Research and Development (AMED) in fiscal year 2019, the product specifications for the mold were determined and non-clinical trial methods were prepared.

### 1.2 Positioning and validity of this clinical trial

This clinical trial is an exploratory investigator-initiated clinical trial with the primary objective of evaluating the biotube formation ability of the test device BTM1 based on in vivo tissue formation therapy.

In this study, non-clinical trials (efficacy, performance, and safety tests) were conducted under the AMED Translational Research Strategic Promotion Program in FY2020, based on the conceptual requirements advised in the medical device pre-development consultation with the Pharmaceuticals and Medical Devices Agency (PMDA) held in November 2019. In addition, in an implantation test using goats, the biotube formation ability of BTM1 was confirmed. Furthermore, a transplantation test of the biotube in goats was conducted (Reference 14), and it was confirmed that the biotube was replaced with vascular tissue in about 3 months and remained patency for 12 months.

Prior to evaluating the efficacy and safety of this treatment in a confirmatory clinical trial, this clinical trial will first verify the biotube formation ability of BTM1 in humans.

### 1.3 Summary of non-clinical studies

The test device does not actually perform any treatment or diagnosis. The biotube made using the test device is used as an implant for treatment. Therefore, the following requirements were placed on the test device and the biotube. The test device must 1) be capable of being implanted subcutaneously, 2) maintain the shape (including the gap between the core and the outer shell) and 3) strength required for biotube formation even after implantation, 4) form a biotube that can be used for surgical bypass surgery after a certain period of implantation, 5) be able to remove the device and 6) the biotube without damage, and 7) be safe as a medical device. The biotube must meet the following requirements: 8) have a shape and quality (including thickness and uniformity) required clinically, 9) have mechanical strength and flexibility, 10) be implantable, 11) after implantation, autologous cells infiltrate the biotube as a scaffold to form tissue similar to autologous blood vessels, 12) not be decomposed or absorbed for the clinically required period, 13) long-term patency is achieved without anastomotic failure at the site of use, and 14) be connectable, and 15) be preserved. Test items considered necessary to verify safety, efficacy, and stability were selected and performed for each requirement of the test device and the biotube. Tests considered necessary were also performed on the sizer, straightening rod, and soaking dish, which are related accessories. All tests were met, and it was confirmed that the test device has appropriate performance, safety, and efficacy for use in humans.

## 1.4 Test Equipment

### 1.4.1 Name and configuration of the test device

The name of this test device is "BTM1", and it consists of a "core", "outer shell" (2 types of symmetrical shapes), an "inner frame" and an "outer frame". There are two types, 40 cm and 55 cm, depending on the length of the biotube to be produced. In addition, it includes a "sizer", a "straightening rod" and an "immersion dish" as accessories.

[Test device: Photo of BTM1 (left: for 55 cm, right: for 40 cm)]

[figure not shown]

[Test device: Structure and size of BTM1 (top: for 55 cm, bottom: for 40 cm)]

[figure not shown]

① Outer shell A ② Outer frame ③ Core ④ Outer shell B ⑤ Inner frame

[Accessories: Sizer photo (left: for 55 cm, right: for 40 cm)]

[figure not shown]

[Accessories: Sizer structure and size (left: for 55 cm, right: for 40 cm)]

[figure not shown]

[Accessories: Photo of straightening rod]

[figure not shown]

[Accessories: Straightening rod structure and size]

[figure not shown]

[Accessories: Photo of soaking dish]

[figure not shown]

[Accessories: Structure and size of immersion dish]

[figure not shown]

#### 1.4.2 display

##### (1) Packaging form

Each box contains one sealed BTM1 in a sterile bag.

##### (2) Exterior labeling

The exterior packaging of the investigational device should indicate that it is for clinical trial use, the clinical trial protocol number, clinical trial identification code, size of the investigational device, manufacturing number, storage method, expiration date, and the name, affiliation, job title, and address of the clinical trial coordinating physician, as follows:

|               |                         |
|---------------|-------------------------|
| 治験用    | 治験実施計画書番号 : B-80        |
| BTM1   |                         |
| (●● cm)       |                         |
| 治験識別記号 : BTM1 |                         |
| 製造番号          | : XXXXXXXX              |
| 保管方法          | : 室温保存                  |
| 使用期限          | : 20XX年XX月XX日           |
| 治験調整医師 |                         |
| 氏名            | : [name]                 |
| 所属・職名         | : 大分大学医学部附属病院 心臓血管外科・医師 |
| 住所            | : [name]   |

#### 1.4.3 Storage and management procedures

The investigational device will be stored at room temperature at each medical institution, avoiding high temperatures and humidity. An investigational device manager will be appointed to ensure the proper storage and management of the investigational device. The investigational device manager will store the investigational device appropriately in accordance with the "Procedures for Management of Investigational Devices," and will create an investigational device management list to keep track of the usage of the investigational device and the progress of the clinical trial.

#### 1.5 A summary of known and potential risks and benefits to subjects

##### 1.5.1 Anticipated risks associated with use of this test device

The implantation of BTM1 and the use of the biotube produced by BTM1 may cause the following malfunctions and adverse events in subjects. Malfunctions that do not directly affect the safety of subjects will be described in the Investigational Device Brochure.

##### (1) Malfunctions and Adverse Events (BTM1)

- Deformation, damage, disintegration, etc. of BTM1 during subcutaneous implantation
- Infection or allergic/anaphylactic reactions due to BTM1 during subcutaneous implantation and associated symptoms (shock, seizures, fever, nausea/vomiting, convulsions, etc.)
- Injury due to physical damage to BTM1 during implantation, implantation, or removal (bleeding, skin injury, subcutaneous injury, perforation, pain and tenderness (head, neck), fractures, etc.)

